### MRI data acquisition

MRI data will be acquired with a 3.0 T magnetic resonance scanner (GE 3.0 T MR750; GE Healthcare, Chicago, IL, USA) with an eight-channel phase-array head coil at the MRI Center in University of Electronic Science and Technology of China. Subjects will be asked to stay awake and to keep their heads still during the scan, with their eyes closed and ears plugged. Subjects will be asked to keep relaxed and not think anything particular during the whole scan. MRI scans will be assessed twice at baseline and after 2 weeks’ intervention or observation period for each patient.

Prior to the rs-fMRI scan, a high-resolution structural image for each subject will be acquired by using a three-dimensional MRI sequence (3DT1) with a voxel size of 1 mm^3^ employing an axial fast spoiled gradient recalled sequence (repetition time 6.008 ms, echo time 1.7 ms, data matrix 256 × 256, field of view 256 × 256 mm^2^). The rs-fMRI images will be obtained with echo-planar imaging (31 contiguous slices with a slice thickness of 5 mm, repetition time 2000 ms, echo time 30 ms, flip angle 90°, field of view 240 × 240 mm^2^, data matrix 64 × 64, total volumes 205). After the rs-fMRI scan, diffusion tensor imaging sequences with single-shot echo planar imaging will be acquired to detect the possible abnormality of the white matter with the following parameters: field of view 256 × 256 mm^2^, repetition time 8500 ms, echo time minimum, matrix = 128 × 128, slice thickness 2 mm, and 78 continuous axial slices with no gap. Two diffusion-weighted sequences will be acquired by using gradient values b = 0 s/mm^2^ and b = 1000 s/mm^2^ with the diffusion-sensitizing gradients applied along 64 non-linear directions.

### Outcome measurement

The clinical evaluations will comprise four components: knee pain, knee function, cognition, and emotion. All evaluations will be performed twice: at baseline and after 2 weeks’ intervention or observation. All evaluations will be evaluated by two trained licensed physicians.

The primary outcome measurements are VAS and the short form of the McGill pain questionnaire of average knee pain in the last 2 weeks and the VAS of knee pain during the MRI scan. The short form of the McGill pain questionnaire could measure the sensory and affective component of pain.

The secondary outcome measurements are the Western Ontario and McMaster Universities Osteoarthritis Index (WOMAC) [27], Attention Test Scale (ATS), Pain Assessment of Sphygmomanometer, Self-rating Anxiety Scale (SAS), Self-rating Depression Scale (SDS), and 12-Item Short Form Health Survey (SF-12). WOMAC could help measure the pain, knee joint function, and quality of life of patients with KOA.

### Data management

The case report form includes observation time points, scanning time points, outcome measures, adverse events, and safety evaluations. The researchers will be required to follow the requirements of the case report form and fill in the relevant information in a timely and accurate manner. Data collection will be performed by study physician, and the quality of the data will be supervised by two independent experienced clinical researchers.

### Data analysis

Before the data analyses, the research group will provide a statistical scheme to the statisticians. The scheme will include the required data and processing method. The data will be processed and analyzed by the statisticians in accordance with the scheme.

For the clinical data, statistical analyses will be performed with SPSS 21.0 statistics software (IBM Corporation, Armonk, NY, USA). The data analysis process will be completed by statisticians who are independent from the research team and blinded to the test settings. A *t* test will be used to compare the numerical variables in the within-group analyses, including the VAS, short form of the McGill pain questionnaire, WOMAC, ATS, SAS, SDS, Pain Assessment of Sphygmomanometer (PAS), and SF-12. Analysis of variance and the Kruskal–Wallis test will be used for numerical variables in the between-group analyses, including age, height, weight, scores of VAS, short form of the McGill pain questionnaire, WOMAC, ATS, SAS, SDS, PAS, and SF-12. The chi-squared test will be used for categorical variables. A two-sided test is applied for available data, and a *P* value of less than 0.05 is considered statistically significant.

The fMRI scan data will be preprocessed and analyzed by SPM12 software (http://www.fil.ion.ucl.ac.uk/spm/) performed on MATLAB 2015b (MathWorks, Inc., Natick, MA, USA). The preprocessing steps will include slice timing correction, head motion correction, spatial normalization, spatial smoothing, and detrending. After data preprocessing, amplitude of low-frequency fluctuation, ReHo, and FC will be used to investigate the cerebral responses of different study groups. Two-sample *t* tests will be used to evaluate possible cerebral responses in each group by within-group analysis (post-treatment minus pre-treatment). We will use between-group analysis to compare the difference in cerebral response changes. Correlation analysis will be conducted to investigate changes between fMRI image data and corresponding clinical data in each group.

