## Design and methods

### Study design

This is a clinical neuroimaging study aiming to investigate the central mechanism of how celecoxib alleviates knee pain for treating KOA. A total of 108 patients with KOA will be randomly allocated to three different groups. Each group includes 36 patients with KOA. The three groups are group A (celecoxib administrated orally once a day), group B (placebo administrated orally once a day), and group C (waiting list). The treatment period will last for 2 weeks. Outcome measurements and MRI scan will be assessed at baseline and at the end of treatment. The changes of clinical variables and cerebral activity of each group will be analyzed after data collection (Fig. 1).

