### Inclusion criteria

Inclusion criteria require that the patients (1) match the diagnosis criteria for KOA set by ACR in 1991 [23], (2) are between 40 and 60 years of age and are right-handed, (3) have not taken any pain killer medicine within 1 month, (4) have at least 3 months of knee pain duration, (5) have an average score on the knee pain Visual Analog Scale (VAS) of at least 3 cm (range of 0 to 10 cm) in the past 2 weeks, (6) have knee joint radiological degree of 0–II in accordance with the Kellgren–Lawrence scale [24], and (7) have signed a written informed consent form.

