### Blinding

As waiting list group without any medical intervention, while the other two groups will be given celecoxib or placebo 200mg daily, it is impossible to blind the patients, clinicians and investigators totally. Patients and researchers of the celecoxib group and the placebo group will be unaware of the assignments until completion of the statistical analysis. Only an independent researcher in the pharmacy department knows the allocation of the celecoxib and placebo groups. The evaluators and statisticians will be blinded to the group allocation during outcome evaluation and data analysis to reduce the risk of bias.

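### Clinical scores are compared across three arms with no baseline covariate and no named celecoxib–placebo contrast; ANCOVA with that contrast would be more precise and easier to interpret

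*Protocol article*

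**What the plan says.** All references are to the protocol article.

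- **Between-group test (Data analysis).** "Analysis of variance and the Kruskal–Wallis test will be used for numerical variables in the between-group analyses", and the list that follows is "including age, height, weight, scores of VAS, short form of the McGill pain questionnaire, WOMAC, ATS, SAS, SDS, PAS, and SF-12". Tests are two-sided at 0.05. Neither a covariate nor a pairwise comparison is named.
- **Within-group test (Data analysis).** A t test "will be used to compare the numerical variables in the within-group analyses", for the same clinical scales.
- **Timing (Outcome measurement).** "All evaluations will be performed twice: at baseline and after 2 weeks’ intervention or observation". A baseline value is therefore collected for every scale.
- **Primary outcomes (Outcome measurement).** "The primary outcome measurements are VAS and the short form of the McGill pain questionnaire of average knee pain in the last 2 weeks", together with VAS knee pain during the scan.
- **Change (Study design).** "The changes of clinical variables and cerebral activity of each group will be analyzed after data collection". This does not say which quantity the between-group tests use.
- **Blinding.** Because the waiting list receives no capsule, "it is impossible to blind the patients, clinicians and investigators totally". The celecoxib and placebo arms are blinded to each other, and so are evaluators and statisticians.
- **Entry (Inclusion criteria).** Patients must "have an average score on the knee pain Visual Analog Scale (VAS) of at least 3 cm", averaged over the preceding 2 weeks.

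**The concern.** The baseline score is already collected and usually predicts the follow-up score. A comparison that does not condition on it discards precision in a trial that may have fewer than 30 evaluable patients per arm.

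A three-arm ANOVA or Kruskal–Wallis test asks only whether any arm differs from the others. Celecoxib against placebo is the one blinded comparison and the one that isolates the drug. The waiting list is unblinded and the primary outcomes are pain ratings. A significant overall P value may therefore come from the waiting list alone, and the article names no contrast that would separate the two explanations.

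At stake are the power of the drug comparison and what a significant clinical result can be taken to mean.

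**Working it through.** **The plan's own figure.** The Sample size section gives 30 per group, raised for 20% dropout to 36: 30 × 1.2 = 36, so 3 × 36 = 108. It states no clinical effect, SD or power, so there is no power figure to reproduce. Losing 20% of 36 leaves 36 × 0.8 = 28.8, and I use 28 per arm.

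**Assumptions not in the article.** Baseline to week-2 correlation r = 0.3, 0.5 or 0.7; a true celecoxib–placebo difference of 0.6 SD; equal SD (set to 1) at both visits and in all arms.

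**1. Precision of the celecoxib–placebo comparison**

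Variance relative to the unadjusted week-2 score:
- week-2 score: 1
- change score: 2(1 − r)
- ANCOVA: 1 − r²

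Power comes from the noncentral t distribution with noncentrality 0.6 / (s × √(2/28)), where s is the square root of the relative variance. For the week-2 score this is 0.6 / 0.267 = 2.24, giving 60% power.

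| r | Variance, change | Variance, ANCOVA | Power, week-2 | Power, change | Power, ANCOVA |
|---|---|---|---|---|---|
| 0.3 | 1.40 | 0.91 | 60% | 46% | 64% |
| 0.5 | 1.00 | 0.75 | 60% | 60% | 72% |
| 0.7 | 0.60 | 0.51 | 60% | 81% | 87% |

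ANCOVA is the most precise in every row. Its margin over the better alternative is 4 points at r = 0.3 (over week-2 scores), 12 at r = 0.5 (over either) and 6 at r = 0.7 (over change scores). In sample-size terms at r = 0.5, 28 per arm with ANCOVA acts like 28 / 0.75 = 37 per arm without it.

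**2. What the three-arm test detects**

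Let celecoxib and placebo have the same mean and the waiting list be worse by d. The noncentrality of the F test is n × Σ(mean − grand mean)² = n × (2/3)d², on 2 and 3n − 3 = 81 degrees of freedom, with critical value 3.11.

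| d (SD, assumed) | Noncentrality, n = 28 | P(significant) |
|---|---|---|
| 0.3 | 1.68 | 19% |
| 0.5 | 4.67 | 46% |
| 0.8 | 11.95 | 87% |

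At 30 per arm the F test gives 20%, 49% and 89%. Simulated Kruskal–Wallis tests at 30 per arm give 46% at 0.5 SD and 88% at 0.8 SD, so the rank test behaves in the same way.

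**3. Within-group tests**

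Entry depends on average VAS over 2 weeks, and a primary outcome is the same measure. To the extent that the screening value serves as the analysed baseline, selection at 3 cm or more lets the mean fall at week 2 in every arm without treatment. The article does not say that the screening value is that baseline, so I attach no size to this.

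**The case against.** **Baseline may already be used.** The Study design section speaks of changes, so the between-group tests may be run on change scores. This stands: a reader might infer that baseline is ignored, and the text does not establish that. It does not remove the point, because change scores are also less precise than ANCOVA at each correlation shown, and the three-arm problem is the same.

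**The contrast may come later.** A separate statistical scheme is to be given to the statisticians, and pairwise comparisons after ANOVA are often specified there. This stands in part. The scheme may add the contrast, but the article does fix the test, and that test is covariate-free and omnibus.

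**The rejection is correct.** If the waiting list truly differs, a significant F test is right. This stands. A reader might take the 19% to 87% as false-positive rates, and they are not. They show how often the P value would be significant without bearing on celecoxib against placebo. Inspecting the arm means would help, but is no substitute for an estimated contrast.

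**Evaluators and statisticians are blinded.** True, but waiting-list patients know that they receive nothing, and VAS and McGill rest on the patient's own report.

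**This is a mechanism study.** The Sample size section says that efficacy is not its focus, which lowers the weight of the point. Pain scores are nevertheless the declared primary outcomes, and clinical improvement enters the planned correlations with brain changes.

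**Two stronger readings fail.** A reader might infer that within-group t tests will be taken as evidence of a drug effect; the article plans them but never says so. A reader might also carry the criticism over to the fMRI analysis, but there the article already states that response changes are compared between groups.

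**Conclusion.** The point holds as one of efficiency and interpretability, not bias. Under randomisation the stated between-group comparison is valid, and any regression to the mean is expected to act alike in all arms.

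The precision gain depends on a correlation that the article does not give. With 28 per arm and a 0.6 SD difference, it is small at r = 0.3 (60% to 64% against week-2 scores) and larger at r = 0.7 (60% to 87%). Against change scores the order reverses: 46% to 64% at r = 0.3, and 81% to 87% at r = 0.7. Selecting patients on VAS tends to lower the correlation within the trial, so the lower part of the range should not be discounted for that scale.

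The lack of a named celecoxib–placebo contrast does not depend on the correlation. How often the three-arm test would be significant because of the waiting list alone depends on the assumed waiting-list deficit: about 19% at 0.3 SD, 46% at 0.5 SD and 87% at 0.8 SD.

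**What to change.** In Data analysis, replace the between-group sentence for the clinical scores with the following:

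1. For each clinical score, fit ANCOVA of the week-2 value on arm, with that score's baseline as covariate.
2. Report the celecoxib-minus-placebo difference with its 95% CI as the main contrast.
3. Report the contrasts with the waiting list as secondary, and label them unblinded.
4. Describe the within-group t tests as descriptive, noting that entry on VAS can produce some regression to the mean in every arm.

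The listed tests can stay for age, height and weight. The change costs one degree of freedom per model and some wording. It needs no new data, visits or patients, and can be made before unblinding.

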### Sample size

The sample size calculation of neuroimaging study is different from that of classic randomized controlled trials. The neuroimaging study focuses on investigating mechanism but not evaluating efficacy. General speaking, in MRI studies, 12 to 15 patients per group provide a statistical result [24, 25]. Our previous literature study shows that at least 20 patients per group can achieve stable results for brain functional network analysis [26]. In this study, we require 30 patients per group in this trial. However, considering a 20% dropout rate and possible excessive head motion during scanning, we will include 36 participants with KOA in each group. Finally, we plan to enroll 108 participants and each group will undergo MRI scans twice to investigate the different central responses among celecoxib, placebo, and waiting list treatment in knee pain KOA patients.

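### The within-group fMRI analysis compares scans of the same patients before and after treatment but is assigned a two-sample t test; it needs a paired or one-sample test

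*Protocol article*

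**What the plan says.** In the protocol article, the fMRI paragraph of Data analysis says: "Two-sample *t* tests will be used to evaluate possible cerebral responses in each group by within-group analysis (post-treatment minus pre-treatment".

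The MRI data acquisition section sets the scan schedule: "MRI scans will be assessed twice at baseline and after 2 weeks’ intervention or observation period for each patient". The same people therefore supply both sets of images in all three groups.

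The sentence after the t test deals with the comparison of groups: "We will use between-group analysis to compare the difference in cerebral response changes". It names no test.

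For the clinical scales, the within-group rule is less specific: "A *t* test will be used to compare the numerical variables in the within-group analyses". It does not say whether that t test is paired. No section mentions a paired or one-sample test for the imaging change.

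**The concern.** A two-sample t test assumes two sets of independent subjects. A pre-to-post contrast within one group has one set of subjects, each measured twice. There are two ways to read the sentence:

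- **Pre and post maps are entered as two samples.** The test ignores the pairing. It uses the variance for independent samples and counts 58 degrees of freedom for 30 patients, where the paired test has 29.
- **Post-minus-pre maps are entered.** Each group then has a single sample, and a two-sample test within the group cannot be carried out.

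The sentence cannot be rescued by reading it as the between-arm test. It refers to analysis within each group, and the between-group step has its own sentence.

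At stake are the maps meant to show how the brain responds in each arm. Scanning each patient twice allows stable differences between patients to be removed from the comparison, and the two-sample test discards that gain. An empty celecoxib map could then reflect the wrong test and not the absence of a response.

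**Working it through.** **The plan's own figure.** Sample size says "In this study, we require 30 patients per group in this trial" and, "considering a 20% dropout rate and possible excessive head motion during scanning, we will include 36 participants with KOA in each group". The arithmetic is 30 × 1.20 = 36 per group and 3 × 36 = 108. Dividing by the retention rate would give 30/0.80 = 37.5, or 38; conversely, 36 × 0.80 = 28.8 patients would remain. The 36 is reproduced and does not bear on this point. The document gives no power, effect size, standard deviation or pre-post correlation for imaging, so there is no stated power to reproduce.

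**Inputs.**
- n = 30 evaluable patients per group (Sample size).
- Two-sided 0.05. The Data analysis section states this level in its clinical-data paragraph; using it for imaging is an assumption.
- ρ, the correlation between a patient's two scans, is assumed from 0 to 0.8.
- Equal variance σ² at both scans, assumed.

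**Formulas for the mean change in one group.**
- Correct (paired) variance: 2σ²(1−ρ)/n, with n − 1 = 29 degrees of freedom.
- Variance used by the two-sample test: 2σ²/n, with 2n − 2 = 58 degrees of freedom.
- Ratio of standard errors, two-sample to paired: 1/√(1−ρ).

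**Effect size.** The true change was set so that the paired test has 80% power at n = 30. This is a mean change of 0.53 standard deviations of the differences. In units of σ it is 0.53 × √(2(1−ρ)); for example, 0.53 × √1 = 0.53 at ρ = 0.5.

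**Simulation, 200,000 data sets per setting, n = 30.**

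| Assumed ρ | SE ratio | Actual type I error, two-sample | Power, two-sample | Power, paired |
|---|---|---|---|---|
| 0 | 1.00 | 5.0% | 81% | 80% |
| 0.3 | 1.20 | 2.1% | 69% | 80% |
| 0.5 | 1.41 | 0.7% | 53% | 80% |
| 0.7 | 1.83 | 0.07% | 25% | 80% |
| 0.8 | 2.24 | 0.01% | 8.5% | 80% |

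The paired test keeps its type I error at about 5% throughout. Power at n = 29 and n = 36, run for ρ of 0.3 to 0.7, is almost the same.

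**Same raw effect at every ρ.** With the change fixed at 0.5σ, the two-sample test stays at 46% to 48% power whatever ρ is. The paired test rises from 47% at ρ = 0 to 61%, 75%, 93% and 99% at ρ = 0.3, 0.5, 0.7 and 0.8. That difference is what the repeated scan offers and the named test gives up.

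**Stricter threshold.** At 0.001, an assumed voxel-type level, an effect with 80% paired power is detected by the two-sample test with 66%, 39% and 8% power at ρ = 0.3, 0.5 and 0.7.

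**The case against.** The best defence concerns weight, and much of it stands.

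- **Role of the test.** The first aim is to compare celecoxib with placebo and waiting list. That is a between-group question, and the disputed sentence does not govern it. Change within an arm cannot separate drug effect from placebo response or the passage of time. The correlation analyses and the primary pain scores are also outside this sentence. This stands, and it limits the error to the within-group maps.
- **It may be a slip of wording.** The reference to post minus pre suggests difference images. An analyst holding those would be forced into a one-sample or paired test, and no power would be lost. This stands as to consequence: the figures above apply only if the two sets of maps are entered as independent samples. It does not make the stated test right.
- **A later statistical scheme may correct it.** Data analysis says one will be given to the statisticians. It may do so, but it would then contradict the published protocol. This is also not a detail left to a fuller document, because the article names a specific test.
- **The size depends on an unknown ρ and a simplified model.** This stands. The loss is nil at ρ = 0, and a single-variable simulation illustrates the mechanism; it does not estimate this trial's voxelwise power.
- **The error is conservative.** This is true for positive ρ: false positives become rarer and real changes are missed.

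**Conclusion.** The concern holds. The protocol names an independent-samples test for a contrast within the same patients, and neither reading makes that correct. If pre and post maps are entered as two samples, the standard error is wrong whenever ρ differs from 0. With ρ between 0.3 and 0.7 it is 20% to 83% too large. Power falls from 80% to between 69% and 25%, and actual type I error falls from 5% to between 2.1% and 0.07%. These figures assume equal variances, 30 patients per group, two-sided 0.05 and a correlation the documents do not supply.

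The effect is confined to the within-group imaging results, where it works by hiding real responses. The sample size rests on customary group sizes with no power calculation, so no documented margin covers the loss. The test should be corrected before the imaging data are analysed.

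**What to change.** Replace the sentence in Data analysis with:

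> Paired t tests (equivalently, one-sample t tests on the post-minus-pre maps) will be used within each group.

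Keep two-sample or analysis-of-variance tests on the difference maps for the between-group comparison only. Use the same wording in the statistical scheme given to the statisticians.

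The cost is one sentence. The scans and sample size are unchanged, and SPM12, the software already named, offers a paired design. The article reports that recruitment was still under way, so the change could be made before analysis.

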As a high prevalence chronic knee pain [11], the prevalence of radiographic knee osteoarthritis was 19% and 28% among adults over 45 years old in Framingham study and Johnston County Osteoarthritis Project [12]. With the aging of the population, most patients with KOA visit a doctor for their pain treatment [13, 14]. KOA has become the leading cause of disability in the world and brings an increasingly high social and economic burden [15, 16]. Meta-analysis has already indicated that celecoxib treatment (200 mg orally once daily) led to significant improvement in the pain and knee function of patients with osteoarthritis [17]. Although celecoxib treatment is effective for pain management in KOA, little is known about how celecoxib treatment modulates the activity of CNS to alleviate pain in patients with KOA.

With the application of neuroimaging techniques in pain research, investigators not only mapped the brain regions which are involved in the central pathogenesis of chronic pain but also can explore the cerebral responses elicited by analgesics so as to illuminate the central mechanism. With resting-state functional magnetic resonance imaging (rs-fMRI), investigators found that the patients with chronic pain demonstrated the alternations in functional connectivity (FC) of medial prefrontal-default mode network and the regional homogeneity (ReHo) value changes of anterior cingulate cortex [18–21].

These results greatly enhance the understanding of the central mechanism of chronic pain and provide a new approach to the research and development of drugs. For instance, Xiaoyan Chen et al. had shown that acupuncture can regulate the descending pain modulatory system of patients with KOA by enhancing the FC between the right frontoparietal network and medial prefrontal cortex [22].

So this trial aims to (1) investigate the influence of celecoxib treatment on the brain activities of patients with KOA compared with that of placebo treatment and waiting list by fMRI and (2) analyze the possible correlations between the changes of cerebral activity and the improvement of clinical variables in each group so as to explore how the celecoxib manages pain by modulating brain function to treat KOA.

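### The between-arm imaging comparison is set on post-minus-pre change with no baseline adjustment named; adjusting for the baseline scan would generally be more precise

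*Protocol article*

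**What the plan says.** The first aim (protocol article, Background) is to "investigate the influence of celecoxib treatment on the brain activities of patients with KOA compared with that of placebo treatment and waiting list by fMRI". The scans that serve it are described under MRI data acquisition: "MRI scans will be assessed twice at baseline and after 2 weeks’ intervention or observation period for each patient". A baseline map therefore exists for every patient.

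Under Data analysis, "amplitude of low-frequency fluctuation, ReHo, and FC will be used to investigate the cerebral responses of different study groups". The response is described as a "within-group analysis (post-treatment minus pre-treatment"), that is, a simple difference of the two scans. The between-arm step is one sentence: "We will use between-group analysis to compare the difference in cerebral response changes". No test, model or covariate is attached to it.

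The same section opens by promising the statisticians a separate statistical scheme, of which it says "The scheme will include the required data and processing method". That scheme is not shown. The planned analysable number is under Sample size: "we require 30 patients per group in this trial".

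**The concern.** The quantity compared between arms is fixed as a change score. A change score forces the slope of the week-2 value on the baseline value to be 1. Where the true slope is below 1, subtracting the whole baseline over-corrects, and two things follow.

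- The contrast is noisier than it need be. The number per arm rests on a literature rule of thumb, with no effect size, SD or power, so the article documents no margin to spare.
- In the one randomisation that is actually carried out, arms of about 30 will differ by chance in baseline signal at some locations. At those locations, raw change tends to move in the opposite direction even without a treatment effect.

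Both matter for a study whose purpose is to say which regions respond to celecoxib rather than to placebo or waiting. The variable that would remedy both is already being collected. The point concerns the imaging model only, not the analysis of the clinical scores.

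**Working it through.** **Inputs from the article.** 30 analysable patients per arm (Sample size). The enrolled 36 reproduces as 30 × 1.20 = 36, and 3 × 36 = 108. These enrolment figures do not bear on this point; 30 is used below.

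**Inputs assumed.**

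- Scan-to-scan correlation rho: not given, so 0.3 to 0.9 is shown.
- Similar variances at the two scans: relaxed in step 5.
- Two-sided 0.05: the article states it in the clinical-data paragraph ("A two-sided test is applied for available data, and a *P* value of less than 0.05 is considered statistically significant") and states no threshold for imaging.
- 80% power for raw change: a reference point only, since the article gives no imaging power.

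**Step 1, variances.** In units of the outcome variance, the patient-level variance is 2(1-rho) for change and 1-rho² for the baseline-adjusted value. The ratio is (1-rho²)/[2(1-rho)] = (1+rho)/2.

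**Step 2, power.** Raw change has 80% power when effect/SE = 1.960 + 0.842 = 2.802. Adjustment multiplies the SE by √[(1+rho)/2], so power is Φ(2.802/√[(1+rho)/2] - 1.960). At rho 0.5: 2.802/√0.75 = 3.235; 3.235 - 1.960 = 1.275; Φ(1.275) = 0.899.

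**Step 3, conditional shift.** Given a baseline difference D between two arms, the change contrast has expectation (true effect) - (1-rho)D. One standard error of a chance difference at 30 per arm is √(2/30) = 0.258 SD. At rho 0.5 the shift is 0.5 × 0.258 = 0.129 SD, opposite in sign to D.

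| rho | variance ratio | SE reduction | adjusted n per arm equal to 30 on raw change | power when raw change has 80% | size of shift when D = 0.258 SD |
|---|---|---|---|---|---|
| 0.3 | 0.65 | 19.4% | 19.5 | 93.5% | 0.181 SD |
| 0.5 | 0.75 | 13.4% | 22.5 | 89.9% | 0.129 SD |
| 0.7 | 0.85 | 7.8% | 25.5 | 86.0% | 0.077 SD |
| 0.8 | 0.90 | 5.1% | 27.0 | 84.0% | 0.052 SD |
| 0.9 | 0.95 | 2.5% | 28.5 | 82.0% | 0.026 SD |

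**Step 4, simulation check.** In 4,000 simulated two-arm comparisons with 30 per arm and no effect, the variance ratios were 0.680, 0.774 and 0.885 at rho 0.3, 0.5 and 0.7, against 0.65, 0.75 and 0.85 in theory. A somewhat higher ratio is expected because the slope is estimated. Putting the simulated ratios into the step 2 formula gives about 92%, 89% and 85% power. Both estimators averaged about zero, so raw change is unbiased over randomisations.

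**Step 5, unequal variances.** With SDs s₀ (baseline) and s₁ (week 2), the change variance minus the adjusted variance is (s₀² + s₁² - 2·rho·s₀·s₁) - s₁²(1-rho²) = (s₀ - rho·s₁)². This is never negative, so apart from the cost of estimating the slope, adjustment does not lose. It is zero when the slope rho·s₁/s₀ equals 1, and there the gain and the conditional shift both vanish.

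**The case against.** The strongest reply is that the article does not say baseline is left out. A reader might infer that the plan specifies an unadjusted model, but the wording does not support that. No model is named, the processing method is deferred to a scheme that is not shown, and a model of change with baseline as covariate would fit the sentence and give the same treatment estimate as an ANCOVA on the week-2 value. This stands: the omission is an inference from silence. What the article does fix is change as the quantity compared, with no adjustment named, and that is enough to ask for the model to be stated.

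A reader might also infer that raw change gives a biased result. It does not: over randomisations it is unbiased with nominal type I error, and its standard error already contains the variability from chance imbalance. The shift in step 3 exists only conditionally on the imbalance that happened to occur.

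Nor can it be said that power is lost at every voxel or connection. The loss depends on the local slope, is about 2 power points at rho 0.9 with similar variances, and disappears where the slope is 1.

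Finally, comparing post-minus-pre maps is a valid and conventional choice, and adjustment is not entirely free, because the covariate differs by voxel. Both are true. They make this a matter of precision rather than validity, but they do not remove the gain.

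**Conclusion.** The point holds as a recommendation on efficiency. The article sets the comparison for its first aim on simple changes and names no use of the baseline scan beyond subtraction. If it is carried out that way, the contrast is valid but generally less precise than the adjusted one.

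In the table, the benefit runs from about 14 power points at rho 0.3 to about 2 at rho 0.9, starting from 80%, and a little less after estimating the slope. These sizes rest on the assumed rho, similar variances at the two scans, 30 analysable patients per arm and a two-sided 0.05 test. The direction does not depend on the value of rho, provided the slope differs from 1 by enough to repay the cost of estimating it. The conditional shift is a second reason to adjust when individual regions are to be interpreted; it is not evidence of a systematic error in the plan.

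**What to change.** In Data analysis, and in the statistical scheme, name the between-group imaging model as an ANCOVA fitted at each voxel, region or connection:

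- outcome: the week-2 value of the measure (amplitude of low-frequency fluctuation, ReHo or FC), or its change, which gives the same contrast;
- factor: arm;
- covariate: the patient's own baseline value of the same measure at the same location.

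Take the celecoxib-placebo, celecoxib-waiting-list and placebo-waiting-list contrasts from that model. Keep the raw-change comparison as a sensitivity analysis.

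The cost is one degree of freedom and a script or tool that accepts voxel-wise covariates in place of the default SPM group menu. No extra scans or patients are needed. The article describes recruitment as under way and says the scheme is supplied before the data analyses, so the wording can be settled in advance. If the scheme already contains this adjustment, one sentence in the article saying so closes the point.
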